## Abstract

**Background:**

Endometriosis is the major cause of progressive pelvic pain and subfertility. Up to 50% of reproductive-age women suffer from pelvic pain. Endometriosis is a classic indication for IVF. Compared with women whose inability to procreate is caused by simple tubal infertility, women with endometriosis often have lower pregnancy rates following in vitro fertilization/intracytoplasmic sperm injection (IVF/ICSI). The administration of gonadotrophin-releasing hormone (GnRH) agonists prior to IVF/ICSI can improve the successful pregnancy rate. Whether a briefer treatment interval would be efficacious has not been studied.

**Methods/design:**

Eligible and consenting women will be randomly assigned to one of two treatments (one cycle of a GnRH agonist or two cycles of a GnRH agonist) prior to IVF/ICSI using a table of random numbers. The primary outcome of this trial is clinical pregnancy rate. Other outcomes include gonadotrophin (Gn) duration, the total dose of follicle-stimulating hormone (FSH) used, number of oocytes retrieved, number of embryos available for transfer, implantation rate, the abortion rate, live birth rate, and incidence of moderate-to-severe ovarian hyperstimulation. The sample size of this trial is estimated to be 421 participants for each of the two arms. Appropriate interim analyses will be conducted by a data monitoring and ethics committee (DMEC), and the final test will be an intention-to-treat analysis.

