## Method

All women who are confirmed to have endometriosis by laparotomy or laparoscopic surgery will visit the reproductive center and receive assisted pregnancy treatment. After the patients enter the IVF/ICSI cycle and establish medical records, the researchers at each center will screen patients who meet the enrollment requirements according to the inclusion and exclusion criteria. The patients will be fully informed about why they were enrolled in the study. If the patients are highly satisfied with the explanation about this research and decide to participate in the study after careful consideration, they will be asked to sign an informed consent form. Patients will understand they could withdraw voluntarily from this clinical study at any time, and the person in charge at each center will provide the patient with their contact phone number. If the patient decides to withdraw, it will be recorded as lost. See Fig. 1.

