#### Early follicular phase long-acting regimen—Ultra-long-acting regimen with one injection

The patient will visit the hospital on menstrual day 2. If the vaginal B-scan ultrasonography does not find cysts and follicles > 10 mm, then 3.75 mg of long-acting GnRHa (Diphereline is the common choice) will be injected. The patient will attend a checkup 28 days after the injection. If ovarian endometriosis is found, then a B-scan ultrasound-guided aspiration biopsy of the cyst will be performed. An intraoperative aspiration of the cyst fluid will be obtained, and saline will be used to repeatedly rinse the cyst cavity. On the same day, B-scan ultrasonography+FSH, LH, E2, and P will be examined. Thirty to 40 days after the injection, patients are expected to reach down-regulation criteria. The down-regulation criteria are E2 < 50 pg/ml, *P* < 0.8 ng/ml, LH < 3 mIU/ml, and endometrium thickness ≤ 5 mm. Then, Gn will be started. See Fig. 3.

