### Data statistics

#### Sample size of participants

This study is a non-inferiority study; that is, it works well when the clinical pregnancy rate does not significantly differ between the two arms. A statistical expert calculated the trial’s sample size based on the existing average IVF cycle outcome across the three reproductive centers and the differences in the outcomes within the existing literature. A total of 401 women in each group will achieve 90% power to detect a non-inferiority marginal difference between group proportions of − 0.0500. The control group proportion is 0.6000. The treatment group proportion is assumed to be 0.5500 under the null hypothesis of inferiority. Power was computed for cases in which the actual treatment group proportion is 0.6500. The test statistic is the one-tailed Z-test (unpooled). The significance level of the test is targeted at 0.0500. The significance level actually achieved by this design is NA [12, 18]. Considering a dropout rate of 5%, we plan to recruit 842 women in total.

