#### Statistical analysis

Statistics will be treated rigorously according to the following steps:

Step 1: Summary of research data

Baseline characteristics and pregnancy results will be summarized, such as number of participants, withdrawal rate. For continuous variables (such as age, FSH level, the number of Gn days, and total Gn dose), mean and standard error will be shown, if the distribution is asymmetric, then median and quartile will be determined. For categoricalvariables (such as clinical pregnancy outcomes), percentage of different groups will be displayed.

Step 2: Comparison between groups

Chi-square test, fisher’s exact test, Mann-Whitney U testor the Kruskal-Wallis test will be usedto determine whether differences in the results of two groups have statistical significance (*p* value < 0.05). Subgroup analysis will be performed according to different degrees of patient’s endometriosis. Endometriosis will be divided into mild degree (grades I and II) and severe degree (grades III and IV) due to the concern of false negatives and false positives.

Step 3: Multivariable analysis and sensitivity analysis

If the baseline data are not balanced between the two groups after randomization, we will adjust the unbalanced factors and perform a multivariable analysis. We will perform sensitivity analysis for loss of follow-up, missing data, which may bias experimental results.

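### The article names only intention-to-treat as the final test of a non-inferiority comparison, with no analysis of departures from the assigned number of injections

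*Protocol article*

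**What the plan says.** The abstract (Methods/design) states that "the final test will be an intention-to-treat analysis". The section on sample size says: "This study is a non-inferiority study; that is, it works well when the clinical pregnancy rate does not significantly differ between the two arms". It sets the margin at -0.05 with a control rate of 0.60, and adds: "The treatment group proportion is assumed to be 0.5500 under the null hypothesis of inferiority". The Aim and the Main research objective also describe a no-worse-than comparison on clinical pregnancy rate.

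The Statistical analysis section names no analysis set. Its third step provides for adjustment if baseline factors are unbalanced, and then: "We will perform sensitivity analysis for loss of follow-up, missing data, which may bias experimental results". Departures from the assigned regimen are not mentioned.

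Three other statements bear on the point:
- Method, on voluntary withdrawal from the study: "If the patient decides to withdraw, it will be recorded as lost".
- One-injection regimen: "Thirty to 40 days after the injection, patients are expected to reach down-regulation criteria". The text does not say how a woman who does not reach the criteria is treated in the analysis.
- Sample size: recruitment is raised for 5% dropout, to 842 women in total.

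**The concern.** In a superiority trial, dilution of the treatment contrast usually works against the claim. In a non-inferiority trial it can work for it. If the new regimen is worse and some women in one arm effectively receive the other arm's regimen, the ITT difference moves towards zero and so away from the margin. A favourable result could then partly reflect departures from the assigned regimen, and no analysis named in the article would show this.

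The article leaves room for such departures. The prescribing doctor is not among those described as blinded and decides the stimulation regimen. One-injection women are only expected to meet the down-regulation criteria. The two-injection lead-in is also longer: its last check falls on day 56-58 (28 + 28 to 30), against day 30-40 for the one-injection arm, a gap of 16-28 days. None of this shows that departures will be common. It does mean that the reader of the final result will want to know whether they mattered.

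**Working it through.** **Inputs (Sample size of participants):** control rate 0.60; assumed true one-injection rate 0.65; margin 0.05; one-sided alpha 0.05; unpooled Z-test; 90% power; 5% dropout. Deviation rates are not given, so 5-30% is assumed.

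**1. The plan's own figure.**
n = (1.645 + 1.282)² × (0.60×0.40 + 0.65×0.35) / (0.05 + 0.05)² = 8.564 × 0.4675 / 0.01 ≈ 400.4, so 401 per arm. This agrees with the stated "A total of 401 women in each group will achieve 90% power". Dropout: 401 × 1.05 = 421.05, so 421 per arm and 842 in total, as stated.

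**2. Dilution at the margin.** Take full-adherence rates of 0.60 v 0.55, and let a share c of the one-injection arm respond like the control arm. The expected ITT difference is -0.05(1 - c).
SE = √((0.24 + 0.2475)/401) = 0.0349.
Chance of declaring non-inferiority = 1 - Φ(1.645 - 0.05c/0.0349).

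| c | 0.05c/SE | Chance |
|---|---|---|
| 0 | 0 | 5.0% |
| 10% | 0.143 | 6.7% |
| 20% | 0.287 | 8.7% |
| 30% | 0.430 | 11.2% |

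At 421 per arm the values are 6.7% (c = 10%) and 8.8% (c = 20%). If the same share crosses over in both arms, they are 8.8% and 14.5%.

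**3. Dilution under the design's own assumption.** With 0.65 v 0.60 and 421 per arm, power is 91.2%. With 10% of the one-injection arm responding like control, its rate is 0.645 and power is 88.5%. Here dilution works against the claim.

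**4. How lost women are counted.** If 5% per arm do not contribute, 842 × 0.95 / 2 = 399.95, about 400 per arm, with 90.0% power. If instead 5% per arm are counted as not pregnant, 421 per arm stay in the analysis. The rates 0.60 v 0.65 become 0.57 v 0.6175, and power is 89.2%. At the margin, 0.60 v 0.55 becomes 0.57 v 0.5225, and the chance of declaring non-inferiority is 5.8%. The two rules differ modestly, but the article does not say which applies.

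**5. Power of a per-protocol test at the design rates.** Excluding 5% leaves 399 per arm: SE = √(0.4675/399) = 0.0342; 0.10/0.0342 - 1.645 = 1.277; power 89.9%. Excluding 10% leaves 378 per arm: power 88.5%.

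**The case against.** The strongest reply is that this is a condensed article. A per-protocol set and a rule for missing outcomes commonly sit in the SAP or full protocol, which are not shown, and naming ITT does not exclude a supporting analysis. This stands as a limit on how firmly the point can be put. What remains is that the article fixes ITT as the final test of a non-inferiority claim, and directs its sensitivity analyses at missing data only.

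The magnitude is also open to challenge. The crossover rates have no source in the article. With crossover, the ITT difference itself lies inside the margin, so the raised percentages are error rates only for the full-adherence effect, not for the ITT effect. At 0.65 v 0.60 dilution lowers power. All of this stands.

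A reader might go further in four ways that the article does not support:
- That the ITT set is not preserved because withdrawals are recorded as lost. That is a status for women who leave the study. No section removes them from the analysis, and the 5% allowance adds recruits; it is not an exclusion rule.
- That cancelled cycles or transfers are protocol deviations. They are foreseen, with reasons to be recorded, and are listed under End of study.
- That withdrawal will differ by arm because the two-injection arm lasts longer. The lead-in does differ, by 16-28 days, but no withdrawal rates are given.
- That non-inferiority must be claimed only if both analyses succeed. This is one convention among several, and per-protocol sets lose the protection of randomisation.

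**Conclusion.** The point holds in a limited form. For a non-inferiority comparison the article names only ITT, and no planned analysis examines departures from the assigned number of injections. If one injection is truly 5 points worse under full adherence, an assumed 10-30% one-arm crossover would raise the chance of a non-inferiority finding from 5.0% to about 6.7-11.2% at 401 per arm. This rests on three assumptions: the crossover rate, deviators responding like the control arm, and interest in the full-adherence effect. Separately, the article does not say how women recorded as lost count in the ITT denominator. The 5% allowance suggests that they are expected not to contribute, but does not say so. Neither matter makes the sample size wrong: 401 and 842 both reproduce.

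**What to change.** Keep ITT as the final test and state its content: all randomised women in their assigned arm form the denominator, and a woman with no transfer counts as not pregnant. State how women recorded as lost are counted, in a way that agrees with the 5% dropout allowance.

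Add a per-protocol analysis of clinical pregnancy, restricted to women who received their assigned number of injections, at the same -5 point margin. Define the set from injection records; a cancelled cycle alone does not remove a woman from it. Report it beside ITT, and say in advance that disagreement between the two will limit the non-inferiority conclusion.

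The cost is some wording and one extra analysis, with no change in the number recruited. Per-protocol power at the design rates is 89.9% if 5% are excluded and 88.5% if 10% are. The per-protocol set is open to selection bias, so it supports ITT and does not replace it.

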**Trial registration:**

This trial has been assigned the following registry number: NCT03006406.

## Plain English summary

Endometriosis is a disease causing progressive pelvic pain and infertility. Up to 50% of reproductive-age women suffer from dysmenorrhea, sexual pain. Surgery or hormone therapy may be meaningful for pain, however, ovary function may be damaged after laparascopy. Progestin and androgen therapy or the oral contraceptive were unhelpful for pragnancy while unexpectedly creating more side effects.

Endometriosis is a classic indication for in vitro fertilization (IVF). Compared with women whose inability to procreate is caused by simple tubal infertility, women with endometriosis often have lower pregnancy rates. The administration of long acting gonadotrophin-releasing hormone (GnRH) agonists prior to IVF/ICSI can improve the successful pregnancy rate. A typical ultra-long-acting regimen may create a low estrogen status of menopause. Such as hectic fever, night sweating and loss of bone mass are significant Whether a briefer treatment interval would be efficacious has not been studied.

Patients were invited to different treatment groups according to random number table. The rest part of IVF treatment along to routine procedure in three reproductive centers.

The top research priorities identified were: the fresh embryo transfer rate, pregnancy rate, total Gn and other indicators; more effective treatments; outcomes and severely affected patients. Least popular priorities were: economic research towards the cost of IVF; and psychological aspects.

In conclusion; individuals affected by endometriosis will have a new view that they could suffer less discomfort and get a live birth quickly. We aimed to provide a safer and more effective ovulation induction regimen for patients with endometriosis.

## Background

Endometriosis is defined as the presence of endometrial-like tissue outside the uterine cavity. This chronic inflammatory condition is estrogen dependent. The incidence and prevalence rates are difficult to quantify because they depend on surgical visualization for a precise diagnosis. Wide ranges have been reported in the literature; 6–10% of reproductive-age woman suffer from endometriosis, women with endometriosis have dysmenorrhea, and up to 50% of women are infertile [9]. Women with pelvic pain identified via endometriosis laparoscopy were followed up; 24–64% of lesions were progressive, and 9–59% were stable over 12 months [15]. The incidence of endometriosis peaks between 25 and 35 years old, which is the greatest period of reproduction [17].

Infertility is common among women with endometriosis. Most reasons are related to chronic pelvic inflammation [5]. Pelvic adhesions can disrupt the pelvic anatomy and alter peritoneal function, fallopian tubal transport is often abnormal, and inflammatory molecules can form under abnormal circumstances that are unfavorable for pregnancy. A tangled anatomy can be repaired via surgery to repair pelvic adhesions and tubal non-function. IVF is a good choice for attempting pregnancy.

Compared with women with tubal infertility, women with endometriosis have lower IVF/ICSI success rates. One meta-analysis that included 22 non-randomized controls reported that the infertility of women with endometriosis was lower than that of those with tubal infertility (odds ratio [OR] = 0.56, 95% confidence intervals [CIs] = 0.44–0.7; [1]). A multivariate analysis also showed that the fertilization and implantation rates of women with endometriosis were significantly lower than those of women receiving the same number of eggs. The low rates of pregnancy and implantation are primarily due to poor egg quality. Poor egg quality leads to a low fertilization rate, which in turn affects the quality of the embryo and affects the implantation rate, especially in patients with severe endometriosis. In oocyte donation cycles, when healthy women donate their disease-free eggs to women with endometriosis, the recipient is associated with comparative endometrial receptivity and pregnancy rates. When the oocytes of women with endometriosis are donated to disease-free women, their implantation rates are lower [6]. Severe endometriosis is associated with a lower pregnancy rate than mild endometriosis (OR = 0.60, 95% CIs = 0.42–0.87; [1]). A meta-analysis provided statistical evidence of the above statement, finding relative pregnancy rates of 0.93 (95% CIs = 0.87–0.99) and 0.79 (96% CIs = 0.69–0.91) among women with mild and severe endometriosis, respectively, through IVF [10].

No clear mechanism has been defined to explain the relationship between endometriosis and subfertility. The complex mechanisms of ovulation, fertilization, tubal pick-up oocyte, and the transport of the embryos or embryo implantation might be partially influenced by hormones [5]. Elevated cytokine and progesterone concentrations in the follicular fluid were found in women with endometriosis [7]. This theory is supported by findings showing concentrations of prostaglandins, proteases, and inflammatory cytokines in the peritoneal fluid of women with endometriosis [2].

As such, reproductive experts have sought to clarify the best IVF treatment protocol for women with endometriosis. The administration of GnRH agonists prior to IVF/ICSI improves the pregnancy rate. The 2006 edition of the Cochrane guidelines recommend the use of 2–6 months of GnRH analogs before the initiation of an IVF cycle to “turn off the inflammatory response”, thereby increasing the pregnancy rate. One meta-analysis that included the randomized controlled trial (RCT) results comparing a general regimen with an ultra-long-acting regimen across three small-scale samples showed that the OR of the pregnancy rate was 4.28 (95% CIs = 2.00–9.15; [13]). Benschop did not find a difference in the pregnancy rates between GnRH agonists and GnRH antagonists administered prior to ART (OR = 0.81, 95% CIs = 0.26–2.54; 67 participants, one trial; [3]). Three additional reviews observed similar benefits for the oral administration of contraceptives versus no treatment [11]; these results require more corroborating evidence. In all cases, the quality of these trials was generally poor, and adequate allocation was concealed. These trials were also generally small, leading to imprecise findings, even when combined in a meta-analysis [4]. The conclusion of the most recent research was that long-term pituitary down-regulation has only a limited effect after including cryopreserved embryo transfers among women with severe endometriosis [16].

A typical ultra-long-acting regimen is to administer 2–3 doses of long-acting Triptorelin prior to ovulation induction to create a low estrogen status of menopause, which allows the ectopic endometrium to atrophy, and ovulation induction is then carried out by gonadotropin (Gn). However, although the patients with endometriosis who use this regimen for ovulation induction can achieve a certain pregnancy rate, the treatment cycle is long, the side effects of low estrogen (such as hectic fever, night sweating and loss of bone mass) are significant, and the use of gonadotropins is high. Therefore, how to ensure a good pregnancy rate while reducing the side effects during the treatment, the treatment cycle, the use of the treatment drug, and the treatment cost has become a focus of ovulation induction research for patients with endometriosis. Whether a briefer treatment interval is efficacious has not been studied [14]. No trials have compared a shorter interval with the typically long protocol.

In this study, we will use an RCT to compare the fresh embryo transfer rate, pregnancy rate, total Gn and other indicators during the ovulation induction application of the ultra-long-acting regimen with one dose or two doses of long-acting Triptorelin in patients with endometriosis, aiming to provide a safer and more effective ovulation induction regimen for patients with endometriosis.

Centers involved in the study:

1. Center for Reproductive Medicine, the First Affiliated Hospital of Zhengzhou University, Zhengzhou, China

2. Jiangxi Provincial Maternal and Child Health Hospital in Nanchang

3. Center for Reproductive Medicine, Third Affiliated Hospital of Zhengzhou University, Zhengzhou, China

## Methods/design

### Aim

In this study, we hypothesis that that the efficacy of using one dose of long-acting GnRH agonist is no worse than that of two doses of GnRH agonist when carrying out IVF-assisted pregnancy for patients with combined endometriosis. At the same time, the treatment cycle is shortened and the total dose of Gn used is reduced.

### Design

A prospective, multicenter, single-blinded, randomized controlled study.

### Main research objective

Clinical pregnancy rate is no worse than that of a control group.

### Secondary research objectives

1. The treatment cycle is shortened.

2. The amount of Gn is reduced.

### Research endpoints

#### Main study endpoint

1. Clinical pregnancy rate (%)

#### Secondary study endpoints

1. Estradiol (E2) level on the day of human chorionic gonadotrophin (HCG) administration

2. Progesterone (P) level on the day of HCG administration

3. The number of oocytes retrieved

4. Gn dosage

5. Gn duration

6. Metaphase II (MII) ratio (during ICSI injection) (%)

7. Two-pronuclei (2PN) ratio (%)

8. Embryos available for transfer

9. Ratio of fresh cycle to transfer cycle (%)

10. Incidence of moderate-to-severe ovarian hyperstimulation syndrome (OHSS) (%)

11. Implantation rate (%)

12. Early miscarriage rate

13. Ectopic pregnancy rate

14. Ongoing pregnancy rate

15. Live birth rate

16. Multiple pregnancy rate

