### Embryo transfer

On the third and fifth days after the eggs are taken, 1–2 embryos or blastocysts will be transferred depending on the quantity and quality of the embryos.

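### The unit of analysis for the MII ratio, 2PN ratio and implantation rate is not fixed, and the listed chi-square and Fisher tests would inflate false positives if run on pooled oocytes or embryos

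*Protocol article*

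**What the plan says.** The protocol article randomises women to one or two injections. Under Secondary study endpoints it lists, each as a percentage, the "Metaphase II (MII) ratio (during ICSI injection"), the "Two-pronuclei (2PN) ratio" and the "Implantation rate". It gives no numerator, denominator or unit of analysis for them. Oocytes retrieved are counted for each woman, and under Embryo transfer "1–2 embryos or blastocysts will be transferred depending on the quantity and quality of the embryos". One woman can therefore supply many oocytes and up to two embryos.

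Under Statistical analysis, Step 1 summarises continuous variables by a mean or median. For categorical variables, with clinical pregnancy as the example, it says that "percentage of different groups will be displayed". Step 2 lists chi-square and Fisher's exact test, and continues: "Mann-Whitney U testor the Kruskal-Wallis test will be usedto determine whether differences in the results of two groups have statistical significance", at p below 0.05. No test is assigned to a named endpoint. Step 3 says that, if baseline data are unbalanced, "we will adjust the unbalanced factors and perform a multivariable analysis". It also plans sensitivity analyses for loss to follow-up and missing data. None of the steps mentions several oocytes or embryos from the same woman.

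**The concern.** Oocytes from one woman share her age, ovarian reserve, stimulation and, for fertilisation, the same sperm source. Two embryos transferred together share one uterus. Their outcomes are therefore likely to be correlated. A chi-square or Fisher test on a two-by-two table of all oocytes or all embryos treats every unit as a separate randomised observation. It understates the variance, so p below 0.05 occurs too often when there is no difference.

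The three endpoints are written as percentages, and Step 1 ties percentages to categorical variables. An analyst could follow the published text, pool the counts and run chi-square without departing from the protocol. A chance difference in maturation, fertilisation or implantation could then be reported as an effect of the shorter down-regulation.

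**Working it through.** **The plan's own figure.** The document gives no figure for these endpoints. Its only calculation is for the primary endpoint, and it reproduces: (1.645 + 1.282)² × (0.60 × 0.40 + 0.65 × 0.35) / (0.05 + 0.05)² = 8.564 × 0.4675 / 0.01 = 400.4, so 401 per group. Adding 5% gives 421 per arm and 842 in total. None of this depends on oocytes or embryos.

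**Inputs for the check.**
- Embryos per woman: 1 to 2 (Embryo transfer).
- Oocytes per woman: not given. Assumed mean 10, with 5 to 12 as the range.
- Intra-woman correlation (ICC): not given. Assumed 0.05 to 0.30 for oocytes and 0.05 to 0.50 for embryos.
- Nominal two-sided level: 5% (Step 2).

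**Formula.** With m units per woman, the design effect is DE = 1 + (m − 1) × ICC. The true type I error of a pooled test at nominal 5% is 2 × [1 − Φ(1.96/√DE)]. The number of women does not enter, so recruiting 842 does not reduce the inflation.

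**Oocytes, m = 10, equal counts.**

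| ICC | DE | 1.96/√DE | True type I error |
|---|---|---|---|
| 0.05 | 1.45 | 1.628 | 10.4% |
| 0.10 | 1.90 | 1.422 | 15.5% |
| 0.20 | 2.80 | 1.171 | 24.2% |

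The mildest case, 5 oocytes and ICC 0.05, has DE 1.20 and 7.4%. The most severe, 12 oocytes and ICC 0.30, has DE 4.30 and about 34.5%.

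**Unequal oocyte counts.** Variation in counts raises the design effect to about 1 + [(1 + CV²) × m − 1] × ICC. The simulation below draws counts with mean 10 and variance 10 + 10²/4 = 35, so CV² = 0.35. The design effect is then 1 + 12.5 × ICC, which is 1.625, 2.25 and 3.50 at ICC 0.05, 0.10 and 0.20. The corresponding type I errors are 12.4%, 19.1% and 29.5%.

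**Embryos.**

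| Mean embryos | ICC | DE | True type I error |
|---|---|---|---|
| 1.5 | 0.05 | 1.025 | 5.3% |
| 1.5 | 0.50 | 1.25 | 8.0% |
| 2 | 0.20 | 1.20 | 7.4% |
| 2 | 0.50 | 1.50 | 11.0% |

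**Simulation.** Data were beta-binomial with no true difference, 2,000 runs per row. The oocyte rows use 401 women per arm, variable counts with mean 10, and a rate of 0.65. The embryo rows use 320 women per arm (about 80% of 401 assumed to reach transfer), 30% with one embryo and 70% with two, and a rate of 0.40.

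| Endpoint type | ICC | Pooled chi-square | Mann-Whitney on per-woman ratios |
|---|---|---|---|
| Oocytes | 0.05 | 11.8% | 4.0% |
| Oocytes | 0.10 | 20.5% | 5.1% |
| Oocytes | 0.20 | 29.8% | 5.1% |
| Embryos | 0.10 | 5.9% | 5.3% |
| Embryos | 0.30 | 7.1% | 4.0% |
| Embryos | 0.50 | 9.5% | 4.9% |

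The Monte Carlo standard error near 5% is √(0.05 × 0.95/2000) = 0.5 percentage points. A second simulation with 421 women per arm and a CV of 0.5 gave 11.4%, 17.0% and 28.1% for pooled oocytes at ICC 0.05, 0.10 and 0.20. A cluster-robust comparison of the same data gave 5.0%, 4.5% and 5.3%.

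**The case against.** The strongest reply is that the protocol never prescribes the invalid analysis. A reader might infer that the plan assigns chi-square or Fisher to these endpoints and treats each oocyte as independent. The text does not say so. It lists four tests together, assigns none of them, and its one example of a percentage is clinical pregnancy, a single outcome per woman. The step from percentage to chi-square is a natural reading, not a stated rule.

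A reader might also infer that no listed method is valid. That is wrong. Reducing the data to one ratio per woman removes the clustering, and Mann-Whitney on those ratios held its level. Giving every woman equal weight is a legitimate choice when women are randomised. The remaining drawback is that the test gives no difference with an interval.

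Three further readings go too far:
- That planned confidence intervals would be too narrow: the section plans none.
- That the protocol presents egg quality as the route by which shorter down-regulation acts: the Background links poor egg quality to endometriosis itself and says that no clear mechanism has been defined.
- That implantation is inflated as badly as the oocyte ratios: with at most two embryos per woman the inflation is modest.

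Finally, an analysis plan that is not shown may settle the unit. Silence on tests could fairly be left to it. But this protocol publishes a list of tests and a significance threshold, and on its natural reading that list admits an invalid analysis for three named endpoints.

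**Conclusion.** The point holds in conditional form. The unit of analysis is not fixed for the three endpoints. If chi-square or Fisher is applied to pooled units, the type I error is about 10% to 30% for the MII and 2PN ratios (10 oocytes per woman, ICC 0.05 to 0.20). For implantation it is about 5% to 11% (1 to 2 embryos, ICC 0.05 to 0.50). Apart from the 1 to 2 embryos, these inputs are assumptions. The direction is certain for any positive correlation; the size is not. The case is strong for MII and 2PN and weak for implantation at low correlation.

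These are secondary endpoints, and neither stated secondary objective (a shorter treatment cycle, less Gn) rests on them. The point is worth correcting but does not threaten the trial's main conclusion.

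**What to change.** Add to Step 2 of Statistical analysis: the MII ratio, 2PN ratio and implantation rate are compared with the woman as the unit, using a GEE or cluster-robust model for the proportion, clustered on woman, and the difference is reported with a 95% CI. State that chi-square and Fisher's test are not used on pooled oocytes or embryos. Mann-Whitney on per-woman ratios would be an acceptable alternative test. Define the numerator and denominator of each ratio in the same place.

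The cost is a few lines of text and a standard procedure. Visits 5 and 7 already record eggs taken, fertilised oocytes, 2PN eggs, embryos transferred and gestational sacs for each subject. The MII count is not itemised there, so confirm that it is captured. The downside is wider intervals for three secondary endpoints than a pooled analysis would give. No more women are needed.
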